## **7.4 Measurement of Further Parameters**

### **Vital signs**

Height, weight, temperature and blood pressure are collected. Height (in cm) is measured at baseline only. Weight (in kg), temperature (in grade centigrade), and blood pressure/pulse are measured at baseline. Oxygen saturation is regularly assessed by pulse oximetry or invasive analysis if applicable.

### **Electrocardiogram (ECG)**

A 12-lead ECG is performed at baseline as well as additionally at the investigator's discretion.

Twelve-lead ECGs is obtained after the patient has been rested in a supine position for at least 5 minutes in each case. The Investigator or designated physician reviews the paper copies of each of the timed 12-lead ECGs on each of the study days when they are collected.

## **8 Ancillary and Post Trial Care**

Study ends for individual patients on day 84 (experimental arm and standard arm without cross over), day 94 (standard arm in case of cross over), or death. A telephone survey of patients (if applicable) or treating physician is conducted weekly after hospital discharge before day 84 (experimental arm and standard arm without cross over) or day 94 (standard arm in case of cross over).

## **9 Assessment of Safety**

### **9.1 Specification of Safety Parameters**

#### **9.1.1 Adverse Events**

According to GCP, an adverse event (AE) is defined as follows: Any untoward medical occurrence in a patient administered a pharmaceutical product and which does not necessarily have a causal relationship with this treatment. An AE can therefore be any unfavorable and unintended sign (including an abnormal laboratory finding), symptom, or disease temporally associated with the use of a medicinal (investigational) product, whether or not related to the medicinal (investigational) product.

An AE may be:

- New symptoms/ medical conditions
- New diagnosis
- Changes of laboratory parameters
- Intercurrent diseases and accidents
- Worsening of medical conditions/ diseases existing before inclusion into the trial
- Recurrence of disease

Increase of frequency or intensity of episodic diseases.

Each AE must be reported only once, indicating the worst CTC (Version 5.0) grade. If an event stops and later restarts, all occurrences must be reported.

A pre-existing disease or symptom is not considered an adverse event unless there is an untoward change in its intensity, frequency or quality. This change is documented by an investigator.

Surgical procedures themselves are not AEs; they are therapeutic measures for conditions that require surgery. The condition for which the surgery is required may be an AE. Planned surgical measures permitted by the clinical trial protocol and the condition(s) leading to these measures are not AEs, if the condition leading to the measure was present prior to inclusion into the trial.

AEs are classified as "non-serious" or "serious".

### **9.1.2 Serious Adverse Event**

A serious adverse event (SAE) is one that at any dose:

- Results in death
- Is life-threatening (the term life-threatening refers to an event in which the patient was at risk of death at the time of event and not to an event which hypothetically might have caused death if it was more severe)
- Requires patient hospitalization or prolongation of existing hospitalization
- Results in persistent or significant disability/incapacity
- Results in a congenital anomaly/birth defect.

Is medically significant (e.g. suspected transmission of an infectious agent via medicinal product). Moreover there are other situations - such as important medical events that may not be immediately life threatening or result in death or hospitalisation but may jeopardize the patient or may require intervention to prevent one of the other outcomes listed above.

### **9.1.3 Expectedness**

An 'unexpected' adverse event is one the nature or severity of which is not consistent with the expected side-effects of Convalescent Plasma Infusions mentioned in 6.3. Furthermore, reports which add significant information on specificity or severity of a known adverse reaction are counted as 'unexpected' events.

### **9.1.4 Suspected Unexpected Serious Adverse Reaction (SUSAR)**

SAEs that are both suspected, i.e. possibly related to IMP, and 'unexpected', i.e. the nature and/or severity of which is not consistent with the applicable product information are to be classified as Suspected Unexpected Serious Adverse Reactions (SUSARs).

In case if either the investigator, who primarily reported the SAE, or the second assessor classify the SAE as 'suspected' ("reasonable possibility" or "unknown", see below) and the SAE is also unexpected, it is categorized as a SUSAR.

All SUSARs are subject to an expedited reporting to the responsible ethics committee(s), the competent authority PEI and to all participating investigators.

## **9.2 Period of Surveillance and Documentation**

All AEs reported by the patient or detected by the investigator are collected during the trial. AEs must also be documented in the patient's medical records. Whenever possible, the investigator records the main diagnosis instead of the signs and symptoms normally included in the diagnoses.

In this trial, **all AEs that occur after signature of the informed consent** are documented on the pages provided in the CRF. AEs must be followed up from first plasma administration up to 28 days after last plasma administration or until all drug-related toxicities have been resolved, whichever is later, or until the investigator assesses AEs as "chronic" or "stable".

Each AE must be reported, indicating the worst CTC (Version 5.0) grade. If an event stops and later restarts, all occurrences must be reported. A specific procedure for definition and reporting of SAEs is described in Section 9.3.

### 9.2.1 Grading of AEs

The grading of AEs in this trial is carried out on the basis of the 5-grade scale defined in the CTCAE v5.0.

|                 |                                                                                                                                                                          |
|-----------------|--------------------------------------------------------------------------------------------------------------------------------------------------------------------------|
| Grade 1: | Mild; asymptomatic or mild symptoms; clinical or diagnostic observations only; intervention not indicated.                                                               |
| Grade 2: | Moderate; minimal, local or noninvasive intervention indicated; limiting age-appropriate instrumental ADL*                                                               |
| Grade 3: | Severe or medically significant but not immediately life-threatening; hospitalization or prolongation of hospitalization indicated; disabling; limiting self-care ADL**. |
| Grade 4: | Life-threatening consequences; urgent intervention indicated.                                                                                                            |
| Grade 5: | Death related to AE                                                                                                                                                      |

A Semi-colon indicates 'or' within the description of the grade.

Activities of Daily Living (ADL)

\*Instrumental ADL refer to preparing meals, shopping for groceries or clothes, using the telephone, managing money, etc.

\*\*Self-care ADL refer to bathing, dressing and undressing, feeding self, using the toilet, taking medications, and not bedridden.

The grading of all AEs listed in the CTCAE v5.0 is based on the information contained therein. The grading of all other AEs, i.e. those which are not listed in the CTCAE v5.0 is performed by a responsible investigator.

### 9.2.2 Coherence between AEs and the IMP

The Investigator must provide an assessment of causal relationship of each of the clinical trial IMPs to each AE according to the following scale:

|                     |                                                                                                                                                                                |
|---------------------|--------------------------------------------------------------------------------------------------------------------------------------------------------------------------------|
| Y (Yes)      | There is a reasonable possibility that the IMP/s caused the AE.                                                                                                                |
| N (No)       | There is no reasonable possibility that the IMP/s caused the AE and other causes are more probable.                                                                            |
| Uk (Unknown) | Only to be used in special situations where the Investigator has insufficient information (i.e., the patient was not seen at his/her centre) if none of the above can be used. |

### 9.2.3 Outcome of AEs

The outcome of an AE at the time of the last surveillance is classified as:

|                                                |                                                                                                                                                                                         |
|------------------------------------------------|-----------------------------------------------------------------------------------------------------------------------------------------------------------------------------------------|
| Recovered/
resolved                 | All signs and symptoms of an AE disappeared without any sequels at the time of the last interrogation.                                                                                  |
| Recovering/
resolving               | The intensity of signs and symptoms has been diminishing and/ or their clinical pattern has been changing up to the time of the last interrogation in a way typical for its resolution. |
| Not recovered/
not resolved         | Signs and symptoms of an AE are mostly unchanged at the time of the last interrogation.                                                                                                 |
| Recovered/
resolved with
sequel | Actual signs and symptoms of an AE disappeared but there are sequels related to the AE.                                                                                                 |
| Fatal                                   | Resulting in death. If there are more than one AE only the adverse event leading to death (possibly related) is characterized as 'fatal'.                                               |
| Unknown                                 | The outcome is unknown or implausible and the information cannot be                                                                                                                     |

supplemented or verified.

### 9.2.4 Action taken

The action taken is assigned to one of the following categories:

|                                  |                                                                                      |
|----------------------------------|--------------------------------------------------------------------------------------|
| Dose not changed          | No change in the dose                                                                |
| Dose reduced              | Reduction in the dose                                                                |
| Temporary discontinuation | Temporary discontinuation of treatment                                               |
| Drug withdrawn            | Discontinuation of treatment                                                         |
| Unknown                   | The information is unknown or implausible and it cannot be supplemented or verified. |
| Not applicable            | The question is implausible (e.g. the patient is dead).                              |

### 9.2.5 Countermeasures

The term 'Countermeasures' refers to the specific actions taken to treat or alleviate adverse events or to avoid their sequels. The following categories are used to categorize the countermeasures to adverse events:

|                       |                                                               |
|-----------------------|---------------------------------------------------------------|
| None           | No action taken                                               |
| Drug treatment | Newly-prescribed medication or change in dose of a medication |
| Others         | Other countermeasures, e.g. an operative procedure            |

## 9.3 Reporting of Serious Adverse Events by Investigator

All SAEs must be reported by the investigator to the responsible Safety Officer at the KKS Heidelberg (on behalf of sponsor) within 24 hours after the SAE becomes known using the "Serious Adverse Event" form. The initial report must be as complete as possible, including details of the current illness and (serious) adverse event as well as an assessment of the causal relationship between the event and the trial medication. The reporting is performed by faxing of a completed 'SAE Form' to the KKS Heidelberg.

**Fax-number: [name]**

## 9.4 Expedited Reporting

SUSARs are to be reported to the ethics committee(s), regulatory authorities and to all participating investigators within regulative defined timelines, i.e. they are subject to an expedited reporting.

All SAEs are forwarded by e-mail immediately (not later than 24 hours after receipt) by the responsible person at KKS Heidelberg to the coordinating investigator or the scientific coordinators in order to perform a second assessment. The coordinating investigator or the scientific coordinators fill out a 'Second Assessment Form' for each SAE and return it by e-mail to the KKS Heidelberg within 48 hours.

**E-mail: [contact]**

The 'Second Assessment Form' contains the following information:

- I) Assessment of relationship between SAE and IMP
- II) Assessment of expectedness of SAE (derived from IB or SPC)
- III) Assessment of relationship between SAE and the underlying disease
- IV) Statement if the benefit/ risk assessment for the trial did change as a result of SAE.

The expedited reporting is carried out by KKS Heidelberg.

## **9.7 Emergency Treatment**

During and following a patient's participation in the trial, the investigator should ensure that adequate medical care is provided to a patient for any AE, including clinically significant laboratory values. The investigator should inform a patient when medical care is needed for intercurrent illness(es) of which the investigator becomes aware.

## **9.7 Events of special interest**

In cases of **transfusion reactions** after plasma transfusion e.g. anaphylaxis or hemolysis or transfusion related lung injury (TRALI), the safety desk of the KKS should be informed immediately by faxing of a completed SAE form (see above).

## **9.8 Deaths**

All deaths that occur during the study, or before EOS, must be reported as follows:

- Death should be documented in the eCRF and should be reported as an SAE.
- Where death is not due (or not clearly due) to SARS-CoV-2, the AE causing the death must be reported to the Safety Officer at the KKS Heidelberg within 24 hours after the death becomes known using the "Serious Adverse Event" form. (9.1.2 Serious Adverse Event). The report should contain a comment regarding the co-involvement of SARS-Cov-2 disease, if appropriate, and should assign main and contributory causes of death

Deaths with an unknown cause should always be reported as a SAE.

# **10 Statistical Considerations**

## **10.1 Study Design**

This is a randomized open-label, multicenter phase-II study in patients with severe SARS-CoV-2 disease subjects

*Randomisation (rf. also to chapter 6.8):*

Randomisation is done either into experimental arm E or into standard arm S in a 1:1 ratio using block randomisation stratified for the factor "patient group", defined by group 1 (patients with hematological malignancies, history of stem cell transplantation and/or active cancer therapy – incl. chemotherapy, radiotherapy, surgery – within the last 24 months or less.), group 2 (drug induced immunosuppression not meeting the criteria of group 1), group 3 (age  $\geq 50$  - 75 years and meeting neither the criteria of group 1 nor group 2 and Lymphopenia  $< 0.8 \times G/I$  and/or D-dimer  $> 1\mu g/mL$  and group 4 (age  $> 75$  years and meeting neither the criteria of group 1 nor group 2).

## **10.2 Analysis Variables**

### **10.2.1 Primary endpoint and primary estimand**

The main purpose of the study is to assess the time from randomization until an improvement within 84 days defined as two points on a seven point ordinal scale or live

discharge from the hospital in high-risk patients (group 1 to group 4) with SARS-CoV-2 infection requiring hospital admission by infusion of plasma from subjects after convalescence of a SARS-CoV-2 infection or standard of care. .

In the Addendum to the ICH E9 guideline (final version), the estimands framework is recommended as clear and transparent definition of “what is to be estimated” (International Council for Harmonization 2019). An estimand is defined through the treatment, the targeted population, the variable, a specification of how to handle intercurrent events (postrandomization events) and a population-level summary. In the following, the primary estimand corresponding to the primary objective is described.

The primary estimand corresponding the primary objective is defined as follows:

**Treatment:** Infusion of frozen CP (on two days of intervention from two different donors) vs. standard of care (as described in 5.7).

**Population:** The targeted population is defined through the in- and exclusion criteria.

**Variable:** Time from randomisation to clinical improvement within 84 days by two points on a seven point ordinal scale or live discharge from the hospital.

**Post-randomisation events:** live discharge from the hospital is incorporated into the variable definition (composite strategy), death from any cause within 84 days after randomization without previous improvement is taken into account by censoring deceased patients at day 84 (see sections 10.3 and 10.5.4 for rationale) ); treatment switch will be ignored (treatment policy strategy, see sections 10.3 and 10.5.4 for rationale); event-free patients at the end of the follow-up period are censored and drop-outs are censored at the last observation (hypothetical strategy).

**Summary measure:** Hypothesis testing is conducted using a log-rank test. The summary measure for effect quantification is the hazard ratio for the endpoint “clinical improvement by two points or live discharge” between the two treatment arms (which is estimated using Cox regression).

### 10.3.2 Secondary Endpoints

Overall survival, defined as the time from randomization until death from any cause

28-day, 56-day and 84-day overall survival rates

SARS-CoV-2 viral clearance and load as well as antibody titres.

Requirement mechanical ventilation at any time during hospital stay (yes/no)

Time until discharge from randomization.

Viral load, changes in antibody titers and cytokine profiles are analysed in an exploratory manner using paired non-parametric tests (before – after treatment).

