### **Objectives**

Primary Objective:

- To assess the time from randomization until an improvement (within 84 days) defined as two points on a seven point ordinal scale or live discharge from the hospital in high-risk patients (group 1 to group 4) with a SARS-CoV-2 infection requiring hospital admission by infusion of plasma from subjects after convalescence of a SARS-CoV-2 infection or standard of care.

Secondary Objectives

1. To assess overall survival, and the overall survival rate at 28, 56 and 84 days.
2. To assess SARS-CoV-2 viral clearance and load, cytokine changes over time as well as antiviral antibody titres.
3. To assess percentage of patients that required mechanical ventilation
4. To assess time from randomization until discharge

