The primary analysis of the trial will compare the Kaplan-Meier curves for the primary endpoint at two-sided significance level of  $\alpha=5\%$ . This will be achieved by using a log-rank test stratified for factor "patient group". The event "death from any cause" will be taken into account by right-censoring deceased patients at the last day of follow-up (day 84).

The fact that some patients from the control group might switch to the experimental group from day 10 will be ignored in the primary analysis. Patients who drop out during the trial or are lost to follow-up are taken into account as censored observations. Analysis will be based on the Full Analysis Population according to the Intention-to-treat principle.

A supplementary analysis of the primary endpoint will involve the inverse probability censoring weighting (IPCW) approach to estimate a treatment effect in the hypothetical scenario that patients from the control group had not switched to the experimental group (Robins & Finkelstein 2000). As another supplementary analysis modeling this hypothetical scenario, a rank preserving structural failure time (RPSFT) model will be fitted (Robins & Tsiatis 1991). Other supplementary analyses include a model by Fine and Gray (1999) targeting the subdistribution hazard for 'clinical improvement by 2 points or live discharge from hospital'.

Further sensitivity analyses of the primary endpoint include an analysis based on the per protocol population.

Secondary outcomes are:

1. Overall survival and survival rates at days 28, 56 and 84
2. Differences in SARS-CoV-2 viral clearance and load as well as antibody titres
3. Percentage of patients that required mechanical ventilation
4. Time until discharge.

Safety: Safety analyses are performed according to established CTCAE guidelines

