### **7.3.3 Laboratory parameters**

Nose/throat swabs are collected at day 0 and day 1 (before first CP administration) and subsequently at day 2, 3, 5, 7, 10, 14, 28 or until discharge. Serum for SARS-Cov-2 diagnostic is collected at baseline and subsequently at day 3, 7, 14 and once during the follow-up period (between day 35 and day 84). Serum collection on the following days is optional: day 1, 2, 3, 10 and 28. Details on sample collection and schedule will be provided in the laboratory manual.

Nasopharyngeal swabs are analysed for SARS-CoV-2 RNA viral load by semi-quantitative real-time RT-PCR in the laboratory of Prof. [name] (Center for Infectious diseases, University Hospital Heidelberg). Patient serum obtained at the different time points is stored

at -20° C until further use. Antibodies directed against SARS-CoV-2 are going to be analysed in recipient serum before (day1) and after (day 3) treatment. IgG Antibodies are detected in standard ELISA tests. Further, analyses for neutralizing antibodies are performed by [name]. [name] (DKFZ, Heidelberg). Cytokine analyses is performed in the laboratory of PD [name] (NCT Heidelberg) with the Bio-Plex Pro Human Cytokine 48-Plex Screening Panel (Biorad, Munich, Germany). To evaluate the effects of CP onto inflammation and cytokine levels, a first analysis is performed after the first randomized 40 patients. All other serum specimens are analyzed at the end of trial.

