#### **10.5.5 Analysis of the Secondary Endpoints**

Overall survival is analyzed by using a Cox regression model adjusting for treatment and patient group, determining hazard ratios with 95% confidence intervals and (descriptive) p-values. Survival estimates are calculated using the Kaplan-Meier method together with 95% log-log-type confidence bands, and the 28-day survival rate will be given for both treatment groups together with 95% confidence intervals. Analogously as for the supplementary analysis of the primary endpoint, an IPCW model and a RPSFT model will additionally be fitted for the secondary endpoint overall survival to assess the potential treatment effect in case patients had not switched from the control to the experimental arm.

Time until discharge will be assessed similarly to the primary endpoint, providing Kaplan-Meier estimates for the cumulative discharge rate for both treatment groups and conducting a log-rank test stratified for the factor “patient group”, and censoring patients who died from any cause at day 84 in analogy to the analysis of the primary endpoint. Analogously as for the sensitivity analysis of the primary endpoint, an IPCW and a RPSFT model will additionally be fitted for the secondary endpoint ‘time until discharge’ to assess the potential treatment effect in case patients had not switched from the control to the experimental arm.

The secondary endpoint “requirement of mechanical ventilation (yes/no)” is analyzed by means of a logistic regression model adjusting for the factors treatment and patient group. Also, absolute and relative frequencies will be given for this endpoint, together with 95% confidence intervals.

The secondary endpoints SARS-CoV-2 viral load and antibody titres will be assessed over time by means of linear mixed models adjusting for treatment group, patient group, and

baseline value as fixed factors, as well as time as repeated factor using an unstructured covariance matrix, calculating least square means estimates and 95% confidence intervals.

While it is indirectly assumed by these models that data will be missing at random, i.e. that the missingness can be explained by observed covariate and outcome values, we will assess the robustness of this assumption by means of sensitivity analyses by means of pattern mixture models assuming that data will be not missing at random.

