For all secondary endpoints, the analysis will be conducted based on the FAS and as a sensitivity analysis based on the per protocol population.

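### Exploratory before-after tests for viral load, antibody titres and cytokines cannot isolate a plasma effect: they are not ranked against the 10.5.5 between-arm model, and cytokines have no other method

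*Protocol*

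**What the plan says.** Three places in the protocol bear on the analysis of these laboratory endpoints.

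- **Section 10.3.2 (Secondary Endpoints)** covers all three families: "Viral load, changes in antibody titers and cytokine profiles are analysed in an exploratory manner using paired non-parametric tests". The contrast is within patient, before versus after treatment. The section does not say which arm is tested and names no comparison of arms.
- **Section 10.5.5 (Analysis of the Secondary Endpoints)** covers two of the three: "The secondary endpoints SARS-CoV-2 viral load and antibody titres will be assessed over time by means of linear mixed models adjusting for treatment group". The model also contains the baseline value, the patient group and time. The section adds: "For all secondary endpoints, the analysis will be conducted based on the FAS". That set contains both randomised arms. Cytokines are not mentioned.
- **Section 7.3.3 (Laboratory parameters)** gives the purpose of the cytokine work: "To evaluate the effects of CP onto inflammation and cytokine levels, a first analysis is performed after the first randomized 40 patients". The assay is a 48-plex panel. For recipient antibodies, the same section plans measurements "analysed in recipient serum before (day1) and after (day 3) treatment".

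The synopsis words the outcome as "Differences in SARS-CoV-2 viral clearance and load as well as antibody titres", which reads as a comparison of arms. Its secondary objectives include cytokines: "To assess SARS-CoV-2 viral clearance and load, cytokine changes over time as well as antiviral antibody titres".

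**The concern.** Viral load, antibody titres and cytokine levels can all be expected to move during an acute infection whether or not plasma is given. A before-after test asks whether a marker changed. It does not ask whether it changed more with plasma than without, so natural course and plasma effect are added together in one number. The trial randomises 1:1, so a concurrent control that removes the natural course is available.

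Two consequences follow. For viral load and antibody titres, two analyses of different contrasts are fixed for the same secondary endpoints, and nothing settles in advance which one is reported as the result. For cytokines, the stated aim is an effect of plasma but the only stated method cannot estimate one. The rationale in sections 6.2 and 10.3 rests on neutralising antibodies, so these results are likely to be read as evidence on mechanism.

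**Working it through.** **Passages compared**

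| Marker | Before-after test (10.3.2) | Between-arm model (10.5.5) | Rule of precedence |
|---|---|---|---|
| Viral load | yes, exploratory | yes | none |
| Antibody titres | yes, exploratory | yes | none |
| Cytokines | yes, exploratory | no | not applicable; only one method |

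The protocol states no effect size, power or sample size for these markers, so there is no figure of its own to reproduce.

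**Inputs for an illustration**

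- From section 10.3: 164 evaluable patients, 1:1, so 164/2 = 82 per arm.
- From section 7.3.3: a first cytokine look after 40 randomised patients, so about 40/2 = 20 per arm.
- Assumed: normal data, pre-post correlation 0.5, the same natural change in both arms, plasma effect exactly zero. The natural change is varied over 0, 0.25, 0.5 and 1.0 baseline SD.
- Tests at two-sided 0.05: a Wilcoxon signed-rank test in the plasma arm, and a Mann-Whitney test of change between arms. There were 2,000 simulated trials per row, so the largest simulation standard error is √(0.5·0.5/2000) = 0.011.

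**Share of trials significant when plasma does nothing**

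| Per arm | Natural change (SD) | Before-after test, plasma arm | Between-arm test |
|---|---|---|---|
| 82 | 0 | 5.8% | 5.3% |
| 82 | 0.25 | 59% | 5.4% |
| 82 | 0.5 | 99% | 4.8% |
| 82 | 1.0 | 100% | 5.3% |
| 20 | 0 | 4.7% | 4.3% |
| 20 | 0.25 | 18% | 5.3% |
| 20 | 0.5 | 54% | 5.1% |
| 20 | 1.0 | 99% | 5.7% |

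**Hand check.** With correlation 0.5, the SD of the change is √(2 − 2·0.5) = 1 baseline SD. The chance of significance is then about Φ(d·√n − 1.96).

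- n = 82, d = 0.25: 0.25·9.06 − 1.96 = 0.30, giving 0.62.
- n = 82, d = 0.5: 0.5·9.06 − 1.96 = 2.57, giving 0.99.
- n = 20, d = 0.25: 0.25·4.47 − 1.96 = −0.84, giving 0.20.
- n = 20, d = 0.5: 0.5·4.47 − 1.96 = 0.28, giving 0.61.

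These normal-theory values are close to the simulation and a little higher where they differ, as expected for a rank test and, at n = 20, a small sample.

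**The case against.** The strongest reply is that section 10.3.2 calls these tests exploratory, and that an exploratory within-patient test can stand beside a between-arm model because the two answer different questions. Much of this holds. The protocol never says that a significant before-after test will be called a plasma effect. For viral load and antibody titres the randomised comparison is planned, with treatment group in the model and both arms in the analysis set. A paired look at recipient antibodies from day 1 to day 3 is also a reasonable description of what happens around the infusions. What the reply does not supply is a statement of which analysis is the result for those two endpoints, or any between-arm method for cytokines.

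A reader might infer three stronger points that the protocol does not support:

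- **That the plan would find a plasma effect with near certainty when there is none.** The rate runs from about 18% to 100% over the non-zero changes and sample sizes above. It rests on assumed drifts, and swabs stop at discharge, so late viral load pairs would be fewer.
- **That the 10.5.5 model forces one constant treatment difference over time.** The section lists no treatment-by-time term, but it does not exclude one, and such detail may properly sit in the SAP.
- **That the control arm is discarded throughout.** As stated methods go, that is true only of cytokines.

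The status of cytokines is itself mixed: they are in the synopsis objectives but not in the secondary objectives of section 2.2 or the synopsis outcome list. That narrows the gap but does not close it, because section 7.3.3 still states an aim about the effect of plasma.

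**Conclusion.** The point stands in a limited form. For viral load and antibody titres, the protocol fixes two different contrasts without ranking them. For cytokines, it fixes only a contrast that cannot answer the stated question, at the 40-patient look and at the end. The primary endpoint, its test and its type I error are untouched, and the exploratory label keeps the matter moderate.

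How far a before-after test could mislead depends on the natural change, which is an assumption here. Under the working assumptions, drifts of 0.25 and 0.5 SD make it significant in about 59% and 99% of null trials with 82 plasma patients, and in about 18% and 54% with 20. The between-arm comparison stays near 5% in every scenario. The conclusion that the paired test cannot separate plasma from recovery does not depend on those figures.

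**What to change.** 1. In section 10.3.2, refer to 10.5.5 and state that its between-arm mixed model is the analysis of viral load and antibody titres. A treatment-by-visit term is preferable, so that the difference between arms is reported by day.
2. In section 10.5.5, add a baseline-adjusted between-arm comparison of change for cytokines, and use it in the look after 40 randomised patients too. Report it as exploratory, given a 48-plex panel and about 20 patients per arm.
3. Delete the paired tests, or label them as within-arm description that supports no claim of a plasma effect.

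The cost is wording in the protocol, carried into the SAP. No new data are needed. The model for viral load and antibody titres is already planned; the cytokine comparison would be new work on samples already collected. Its estimate is less precise than a within-arm one: with equal arms the standard error of a difference in mean change is √2, about 1.4 times, that of the mean change in one arm, before any gain from baseline adjustment.
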